### Variables

#### Overview

The study population is those with CLD as an index condition, as defined in the inclusion criteria. The variables will be curated for the identification of CLD-related codes in the computerized medical records of adults registered in the RSC network (Multimedia Appendix 1).

Comparisons will be conducted between population subgroups with different CLD etiologies, sociodemographic characteristics, complications, and comorbidity profiles.

The outcome of the first objective will be the coverage rates of Hep A vaccination among those with CLD.

For the second objective, we will explore significant independent predictors of the following outcomes among those with CLD: (1) one dose of Hep A vaccination and (2) two doses of Hep A vaccination.

Hep A vaccination, as defined by the UK vaccination scheme, includes an initial 0.5 mL for 1 dose, followed by a booster dose of 0.5 mL after 6-12 months. The booster dose may be delayed by up to 3 years if not given after the recommended interval following the primary dose [8]. For this study, we will report boosters administered within 12 months of the first dose for the base case analysis and 3 years from the first dose for a sensitivity analysis. Hep A vaccination in the United Kingdom is available as a monovalent vaccine, as a combined Hep A and hepatitis B vaccine, and as a Hep A and typhoid vaccine [7]. We will consider any Hep A vaccination type as an outcome.

#### Covariates

Sociodemographic characteristics will be reported closest to the earliest date of CLD diagnosis as baseline, within a 10-year range for time-sensitive variables. These include age, gender, ethnicity (categorized into White, Black, Asian, multiracial, and other), rurality (measure of population density), region, socioeconomic status (measured using the index of multiple deprivation), obesity, alcohol consumption, and smoking. A history of comorbid conditions and complications will be extracted from 10 years of computerized medical records, including osteoporosis, bile duct and colon cancers, renal disease (including calculi), ascites, liver failure and transplant, and cardiometabolic disease. The CMMS will be used to report on comorbidity profiles [26,27].

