## Methods

### Study Design

This is a retrospective cohort study using data from the nationally representative Primary Care Sentinel Cohort (PCSC) of the Oxford-Royal College of General Practitioners (RCGP) Research and Surveillance Centre (RSC) [14]. The RSC is one of Europe’s oldest sentinel systems, and hepatitis is one of its 32 monitored conditions [15]. The database has previously been used for liver disease and hepatitis research [3,16].

We will use electronic health record data for the period between January 1, 2012, and December 31, 2022. Data will be extracted retrospectively at the time of the beginning of the study.

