#### Reporting Predictors of 1 and 2 Doses of Hep A Vaccination in People With CLD

##### Overview

A multistate model will be used on a retrospective cohort of individuals identified in the ORCHID diagnosed with CLD. People enter the study on the first diagnosis of CLD, and we will model the transition probabilities between the identified states: diagnosed with CLD, first dose of Hep A vaccination, second dose of Hep A vaccination, and death (Figure 2).

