**Figure 2 figure2:**

State transition diagram for competing risks multistate model for a retrospective cohort of adults with chronic liver disease (CLD) in England between January 1, 2012, and December 31, 2022, evaluating hepatitis A (Hep A) vaccination with 1 and 2 doses as outcomes and death as a competing risk represented as an absorbing state.

A multistate survival model will be fitted to estimate the transition probabilities between the 4 identified study states (Figure 2). The states are (1) diagnosis of CLD, (2) first dose of Hep A vaccination, (3) death, and (4) second dose of Hep A vaccination. The outcome of interest is the Hep A vaccination. Therefore, the state of a second dose of Hep A vaccination is a censored state, with no further transitions to death; the moment a patient receives 2 doses of Hep A vaccination, the follow-up ends. Death is an absorbing state, with no further transitions allowed. Death is included as a competing risk for vaccination, not as an outcome. This means that when calculating the transition probabilities to vaccination, we adjust for when a person is not vaccinated because of death before vaccination rather than for any other predictors of nonvaccination.

Patients lost to follow-up will be right censored and evaluated accordingly as per the likelihood function of the “msm” R package [30].

Multistate probabilities are based on the same assumptions as a Markov process:

The health states considered in the model are thorough and mutually exclusive.The probability to move from one health state to following states only depends on (is conditioned on) the health state of the individual at transition time (memoryless process).Transition probabilities are steady over time.

The state transition probabilities will be estimated conditional on the study risk factors. Study risk factors include (1) etiology of CLD (eg, ALD, CH-B, CH-C, and NAFLD); (2) sociodemographic characteristics (eg, age, sex, ethnicity, deprivation, obesity, smoking, and alcohol consumption); (3) CLD complications (eg, bile duct and colon cancers, renal disease, ascites, liver failure and transplant, and cardiometabolic disease); and (4) comorbidities (eg, CMMS, bile duct and colon cancers, at least 3 doses of COVID-19 vaccine, and flu vaccination).

The multistate model will be estimated using the “msm” (version 1.6.9) package in R [31].

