##### Missing Data

Descriptive analyses will be conducted on the overall study population and applicable subgroups. Data that are not documented in our database will be reported as missing.

Missing data will be presented as a separate category in univariate statistics and compared to the reference category through univariate odds ratios. Missing data categories will be imputed to the reference category if no significant differences are found in the reference category. Missing data categories will be otherwise included in the analysis as an independent category if evidence suggests they are not missing at random; for example, significant differences to the reference category exist.

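### Baseline obesity, smoking and alcohol are taken closest to diagnosis with no limit to values before diagnosis or before the first dose, so follow-up values can enter as baseline predictors

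*Protocol article*

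**What the plan says.** The Covariates section fixes the selection rule: "Sociodemographic characteristics will be reported closest to the earliest date of CLD diagnosis as baseline, within a 10-year range for time-sensitive variables". The variables it lists include "obesity, alcohol consumption, and smoking". The next sentence has a separate rule for clinical history: "A history of comorbid conditions and complications will be extracted from 10 years of computerized medical records".

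Time zero is set in the Overview on predictors of 1 and 2 doses: "People enter the study on the first diagnosis of CLD". The text below Figure 2 makes the covariates predictors of every transition: "The state transition probabilities will be estimated conditional on the study risk factors". On death it says: "Death is included as a competing risk for vaccination, not as an outcome".

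Study Design gives the data period: "We will use electronic health record data for the period between January 1, 2012, and December 31, 2022".

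Missing Data then says: "Missing data will be presented as a separate category in univariate statistics and compared to the reference category through univariate odds ratios". A missing category that does not differ significantly is merged into the reference category. One that does differ stays as its own category.

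**The concern.** A baseline predictor in a time-to-event model should be known at time zero, which here is the first CLD diagnosis. A nearest-value rule with no direction does not secure this, in three ways.

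- A value recorded at or after the first dose can be used to predict that dose.
- Weight, drinking and smoking may change because of the diagnosis, so values from before and after it are mixed under one label.
- Someone with no earlier record acquires a value only by remaining alive and registered until the next one. Having no value then marks short follow-up, and the Missing Data rule either reports that as a predictor category or blends it into the reference group.

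The second objective is to identify predictors of vaccination, and the Discussion intends to use any disparities to target interventions. An artefact in the covariate categories would feed directly into that.

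**Working it through.** **No plan figure to reproduce.** The protocol gives no number for this rule and no recording, death, deregistration or vaccination rates. All sizes below rest on assumptions.

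**From the documents.** Time zero is first diagnosis; diagnoses run from 2012 to 2022 (11 years); the window is 10 years; follow-up ends on 31 December 2022.

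**Assumed.** Records of a variable arise at rate r = 0.1, 0.3 or 0.5 per year, equally before and after diagnosis. Yearly hazards are 5% for first dose, 6% for death and 5% for deregistration. Everything is independent, diagnosis dates are uniform over the 11 years, and the covariate has no effect. I simulated 2 million people per scenario.

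**Step 1: missing under a backward-only rule.** With a full look-back the share is exp(-10r):
- r = 0.1: exp(-1) = 37%
- r = 0.3: exp(-3) = 5.0%
- r = 0.5: exp(-5) = 0.7%

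If records start in 2012, the look-back is the shorter of 10 years and the time since 1 January 2012. The average share is [(1 - exp(-10r))/r + exp(-10r)]/11:
- r = 0.1: (6.321 + 0.368)/11 = 61%
- r = 0.3: (3.167 + 0.050)/11 = 29%
- r = 0.5: (1.987 + 0.007)/11 = 18%

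**Step 2: two-sided against backward-only.** The death-rate ratio, first-dose rate ratio and coverage columns refer to the two-sided rule.

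| r; records used | values after diagnosis | vaccinated with a value: value after dose 1 | missing, two-sided → backward-only | death-rate ratio, missing/recorded | first-dose rate ratio, missing/recorded | crude coverage, missing vs recorded |
|---|---|---|---|---|---|---|
| 0.1; full look-back | 31% | 17% | 26% → 37% | 1.5 | 1.00 | 0.135 vs 0.176 |
| 0.3; full look-back | 38% | 13% | 2% → 5% | 2.2 | 1.00 | 0.093 vs 0.167 |
| 0.5; full look-back | 42% | 10% | 0.2% → 0.7% | 2.9 | 0.98 | 0.069 vs 0.166 |
| 0.1; from 2012 | 42% | 26% | 41% → 61% | 1.7 | 1.00 | 0.153 vs 0.174 |
| 0.3; from 2012 | 45% | 18% | 9% → 29% | 3.0 | 1.01 | 0.118 vs 0.171 |
| 0.5; from 2012 | 46% | 13% | 3% → 18% | 5.0 | 1.00 | 0.081 vs 0.168 |

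Backward-only selection brings the death-rate ratio to about 1.0 in every row. For people diagnosed in 2012, if only 2012-2022 records count, roughly 80% of values fall after diagnosis at r = 0.3 to 0.5.

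**Step 3: effect on the missing-category test.** I take the univariate odds ratio to be for vaccination. With no covariate effect, each recorded category has the same coverage, so missing against reference under full look-back gives:
- r = 0.3: (0.093/0.907)/(0.167/0.833) = 0.103/0.200 = 0.51
- r = 0.1: (0.135/0.865)/(0.176/0.824) = 0.156/0.214 = 0.73

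Both are artefacts of shorter follow-up.

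**Step 4: when the first-dose rate is affected.** If half of first doses also trigger a record of the variable, the first-dose rate ratio, missing against recorded, falls to about 0.4-0.6. Change in behaviour after diagnosis was not simulated.

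**The case against.** **The text is silent; it does not say either side.** It calls the value baseline, and the next sentence uses look-back language for clinical history, so a look-back may have been intended. A condensed article may leave the exact window to a fuller document. What stands: the intention is possible. But the article does state a selection rule, that rule has no direction, and the look-back wording belongs to different variables. Someone coding the sentence as written would take the nearest value on either side.

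**A reader might infer that many baseline values are in fact recorded after diagnosis, and some after vaccination.** The documents cannot support that, because they give no recording rates. The simulation also gives no weight to values recorded on the diagnosis date, which a nearest-value rule would choose first. With full look-back at 0.3-0.5 records per year, the post-diagnosis values lie a median of only 0.6-0.85 years after diagnosis; gaps of several years are a tail.

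**A reader might infer that the estimated predictors of the first dose are biased.** With recording independent of vaccination, the first-dose rate ratio stays at about 1.0. The lower crude coverage reflects shorter follow-up, which a censored time-to-event model handles. This objection holds. It does not protect the death transition, the comparisons by vaccination status or the odds-ratio test, none of which is repaired by censoring in the dose-1 transition.

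**The missing group may be tiny.** At 0.5 records per year with full look-back it is 0.2%, and the high death ratio then describes very few people. This also stands. The death ratio of 5 arises only if records start in 2012.

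**Conclusion.** The concern holds in a limited form. As written, the rule admits values from follow-up, including after vaccination, as baseline predictors in a model whose clock starts at diagnosis. Under 0.1 to 0.5 records per year, about 30-45% of values would be post-diagnosis, and people without a value would have about 1.5 to 5 times the death rate of those with one, together with lower crude coverage, although the covariate has no effect.

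The harm shown is to the death transition, to the crude comparisons by vaccination status in the Statistical Analysis section, and to the Missing Data test. Bias in the first-dose rate is conditional: it needs recording tied to vaccination visits, or lifestyle change following diagnosis. The documents establish neither. If recording before diagnosis is nearly complete, the missing-group problem becomes negligible, but a large share of values may still postdate diagnosis. Characteristics that do not change over time are little affected.

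**What to change.** In Covariates, define the baseline value of each time-sensitive variable as the most recent record on or before the earliest CLD diagnosis date, within a 10-year look-back. Allow at most a short, stated grace period after diagnosis, and never a value recorded after any hepatitis A dose. Code it as missing otherwise. State that records before 2012 may be used for this look-back, and reconcile this with the data period in Study Design. Keep the two-sided value as a sensitivity analysis.

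This is one extraction rule, to be settled before extraction. The cost is more missing values. With full look-back, missingness rises from about 2% to 5% at 0.3 records per year, and from 26% to 37% at 0.1. If records start in 2012, it is about 18-29%, against 3-9% two-sided, at 0.3-0.5 per year. In that last case missingness also follows the year of diagnosis, and hence length of follow-up, so the Missing Data test would again pick up an artefact. That is why the pre-2012 look-back should be written into the rule.

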### Study Size

Age-standardized incidence rates for CLD worldwide are reported as 20.7/100,000 [28]. The RSC network comprises a nationally representative sample of 7.4 million registered patients. This brings an estimate of up to 1656 potential patients with CLD per year of study to be included in our final study population. This is consistent with previous reports on the CLD population in the RSC network [29].

In the United States, Hep A vaccination coverage is reported to range between 10% and 50% [2,9]. Therefore, we expect between 165 and 828 individuals to be found to have both the index condition and outcome of interest per year for a 10-year study period.

The study population will be categorized and stratified for analysis following the CONSORT (Consolidated Standards of Reporting Trials) diagram (Figure 1).

**Figure 1 figure1:**
[figure not shown]
Consolidated Standards of Reporting Trials diagram for eligible individuals in the Research and Surveillance Centre (RSC) network for a retrospective cohort analysis of adults with chronic liver disease (CLD) in England between January 1, 2012, and December 31, 2022, evaluating hepatitis A vaccination with 1 and 2 doses as outcomes.

### Statistical Analysis

#### Reporting Hep A Vaccination Coverage in People With CLD

Hep A vaccination rates will be calculated using the number of vaccinated people with CLD as the numerator and estimates of the CLD population in the ORCHID data set as the denominator. Baseline characteristics of each study group (eg, age and gender) will be summarized using descriptive statistics, including measures of dispersion (eg, SDs and IQRs).

To compare individual characteristics by vaccination status (eg, CLD disease type, sociodemographic characteristics, complications, and comorbidities), we will use descriptive statistics, with pairwise comparisons using the chi-square or Fisher exact tests for categorical variables and the *t* test or Wilcoxon test for continuous variables. If stratification involves more than 2 groups, differences across groups will be tested using the Kruskal-Wallis test for continuous variables and the Pearson chi-square test for categorical variables, followed by pairwise comparisons as above described. All statistical tests will be 2-sided with *P*<.05 considered statistically significant.

#### Reporting Predictors of 1 and 2 Doses of Hep A Vaccination in People With CLD

##### Overview

A multistate model will be used on a retrospective cohort of individuals identified in the ORCHID diagnosed with CLD. People enter the study on the first diagnosis of CLD, and we will model the transition probabilities between the identified states: diagnosed with CLD, first dose of Hep A vaccination, second dose of Hep A vaccination, and death (Figure 2).

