**Methods:**

We will conduct a retrospective cohort study with data from the Primary Care Sentinel Cohort of the Oxford-Royal College of General Practitioners Clinical Informatics Digital Hub database, which is nationally representative of the English population. We will include people aged 18 years and older who have been registered in general practices in the Research and Surveillance Centre network and have a record of CLD between January 1, 2012, and December 31, 2022, including those with alcohol-related liver disease, chronic hepatitis B, chronic hepatitis C, nonalcohol fatty liver disease, Wilson disease, hemochromatosis, and autoimmune hepatitis. We will carefully curate variables using the Systematized Nomenclature of Medicine Clinical Terms. We will report the sociodemographic characteristics of those who are vaccinated. These include age, gender, ethnicity, population density, region, socioeconomic status (measured using the index of multiple deprivation), obesity, alcohol consumption, and smoking. Hepatitis A vaccination coverage for 1 and 2 doses will be calculated using an estimate of the CLD population as the denominator. We will analyze the baseline characteristics using descriptive statistics, including measures of dispersion. Pairwise comparisons of case-mix characteristics, comorbidities, and complications will be reported according to vaccination status. A multistate survival model will be fitted to estimate the transition probabilities among four states: (1) diagnosed with CLD, (2) first dose of hepatitis A vaccination, (3) second dose of hepatitis A vaccination, and (4) death. This will identify any potential disparities in how people with CLD get vaccinated.

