### Objectives

The objectives of this study are as follows:

To report yearly Hep A vaccination coverage in people with CLD by:sociodemographic characteristics (eg, age, sex, ethnicity, deprivation, BMI category, smoking status, and alcohol consumption)etiology of CLD (eg, ALD, CH-B, CH-C, and NAFLD).CLD complications (eg, renal disease, ascites, liver failure and transplant, and other cardiometabolic diseases, including diabetes and heart disease)comorbidities and exposures (eg, Cambridge Multimorbidity Score [CMMS], bile duct and colon cancers, at least three doses of COVID-19 vaccine, and flu vaccination).To report the predictors of 1 and 2 doses of Hep A vaccination in people with CLD.

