### Study Population

We will include adults registered in general practices within the RSC network with a diagnosis of CLD, as defined by our ontology, within the period between January 1, 2012, and December 31, 2022. The following inclusion criteria will be applied: (1) people registered in the RSC general practices, aged 18 years and older, with a diagnosis of CLD; and (2) the ontology for CLD includes ALD, CH-B, CH-C, NAFLD, Wilson Disease, hemochromatosis, autoimmune hepatitis, primary sclerosing cholangitis, and primary biliary cholangitis [2-4].

The following exclusion criteria are applied: (1) patients with recorded contraindications to the Hep A vaccine (confirmed anaphylactic reaction to a previous dose of Hep A containing vaccine or to any of its components); and (2) records of administration of postinfection or risk-of-infection immunoglobulins.

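### The multistate model has no starting state for people who already hold hepatitis A doses at CLD diagnosis, and the yearly coverage denominator is left open

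*Protocol article*

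**What the plan says.** **Predictor model (objective 2).** The Overview under Reporting Predictors sets time zero: "People enter the study on the first diagnosis of CLD, and we will model the transition probabilities between the identified states". The text under Figure 2 lists the states: "The states are (1) diagnosis of CLD, (2) first dose of Hep A vaccination, (3) death, and (4) second dose of Hep A vaccination". It also assumes that the states are exhaustive and mutually exclusive.

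**Data window.** Study Design says: "We will use electronic health record data for the period between January 1, 2012, and December 31, 2022". Covariates allows a 10-year history for time-sensitive baseline variables and comorbidities, but says nothing comparable about vaccine doses.

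**Doses before diagnosis.** Study Population excludes people for vaccine contraindication and for immunoglobulin records, not for earlier hepatitis A vaccination. Earlier vaccination is not among the covariates or the model's risk factors. Combined hepatitis A/B and hepatitis A/typhoid products count: "We will consider any Hep A vaccination type as an outcome".

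**Coverage (objective 1).** The objective is "To report yearly Hep A vaccination coverage in people with CLD". The rate is to be formed "using the number of vaccinated people with CLD as the numerator and estimates of the CLD population in the ORCHID data set as the denominator". No date rule is given for numerator or denominator. Study Population requires people "with a diagnosis of CLD, as defined by our ontology, within the period between January 1, 2012, and December 31, 2022", while the Abstract includes those who "have a record of CLD between January 1, 2012, and December 31, 2022".

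**The concern.** Some people will have been vaccinated before their CLD was diagnosed, for example for travel or because of another risk. Someone with one dose at diagnosis fits both the diagnosis state and the first-dose state, so the model's own assumption of exclusive states fails. The entry rule as written puts that person in the undosed state.

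Three errors can follow:

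- A person who needs no further dose adds time at risk but can contribute no event, which lowers the dose-1 rate.
- A booster given after diagnosis may be recorded as dose 1. This adds a false dose-1 event.
- The same person then has a completed course on record as an incomplete one, and stays at risk of a dose 2 that is not due. This lowers the dose-2 rate.

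Both outcomes of objective 2 are affected. The study's stated purpose is to find disparities, so the more serious consequence is differential error. A group that was better vaccinated before diagnosis would look less likely to be vaccinated after it.

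The coverage question is separate. Yearly coverage can be read as a time trend, and whether a trend means anything depends on who is in each year's denominator.

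**Working it through.** **The plan's own figure.** Study Size gives 1656 people with CLD per year. 20.7/100,000 × 7.4 million = 1531.8, whereas 20.7/100,000 × 8 million = 1656.0. The figure therefore uses the Abstract's 8 million and not the 7.4 million in its own paragraph. That is a separate matter. What counts here is that 10% and 50% of 1656 (165.6 and 828) apply coverage to one year's newly diagnosed people. The protocol gives no uptake rate, death rate or share vaccinated before diagnosis, so those below are assumptions.

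**1. Dose-1 rate when earlier doses are ignored.** Let p0 be the share vaccinated before diagnosis and not dosed again, h the true dose-1 rate in the others, and follow-up u uniform on 0 to 11 years, with no death.

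- A = mean of 1 − exp(−hu) = 1 − (1 − exp(−11h))/(11h)
- Events = (1 − p0)A
- Time at risk = (1 − p0)A/h + 5.5·p0
- Estimated rate ÷ true rate = events ÷ (h × time at risk)

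Example, h = 0.05 and p0 = 0.20: A = 1 − 0.42305/0.55 = 0.2308. Events = 0.1847. Time at risk = 3.693 + 1.100 = 4.793. Ratio = 0.1847/(0.05 × 4.793) = 0.77.

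| p0 | h = 0.02 | h = 0.05 | h = 0.10 |
|---|---|---|---|
| 5% | 0.95 | 0.94 | 0.93 |
| 10% | 0.89 | 0.88 | 0.87 |
| 20% | 0.79 | 0.77 | 0.74 |
| 30% | 0.68 | 0.66 | 0.63 |

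**2. Effect on a comparison.** Take two groups with the same true rate h = 0.05, one with p0 = 5% and the other with p0 = 20%. The apparent rate ratio is 0.77/0.94 = 0.82, with no true difference.

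**3. Yearly coverage under constant uptake.** With uniform entry, dose-1 rate h and death rate d, coverage among those alive after T years of accrual is

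1 − [(1 − exp(−(h+d)T))/(h+d)] ÷ [(1 − exp(−dT))/d].

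With h = d = 0.05:

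- T = 1: 1 − 0.9516/0.9754 = 2.4%
- T = 11: 1 − 6.671/8.461 = 21.2%

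Other denominators that the text allows, at h = 0.05:

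| Denominator | 2012 | 2022 |
|---|---|---|
| Accumulating new cases, d = 0.05 | 2.4% | 21.2% |
| By diagnosis year, followed to end 2022, no death | 40.8% | 2.5% |
| 20 further years of earlier diagnoses, d = 0.05 | 32.5% | 39.4% |
| 20 further years of earlier diagnoses, d = 0.10 | 27.3% | 30.9% |
| Dose 1 within 12 months of diagnosis, 1 − exp(−0.05) | 4.9% | 4.9% |

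The same constant uptake gives a steep rise, a steep fall, a modest rise or a flat line, depending only on the denominator.

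**The case against.** The strongest reply is that the entry rule belongs to the predictor model and that coverage has its own definition. This stands. A reader might infer that vaccinations before diagnosis are lost from coverage, and that yearly coverage must rise by construction. The documents support neither:

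- The coverage numerator is vaccinated people with CLD, and nothing requires the dose to follow diagnosis.
- The denominator is an estimate of the CLD population, not expressly the accumulating cohort. The Abstract's wording allows long-standing cases.
- Study Size works from newly diagnosed people, which leans towards an incident reading, but it fits separate yearly cohorts as well as an accumulating one.

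A reader might also put a size on lost coverage. With 15% vaccinated after diagnosis and 5% to 15% before it, (1 − p0) × 0.15 gives 14.25% to 12.75% counted, against p0 + (1 − p0) × 0.15 = 19.25% to 27.75%, a shortfall of 26% to 54%. This needs earlier doses to be barred from the numerator, which is not stated, and nobody previously vaccinated to be dosed again. It is a worst case built on assumed rates.

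Nor does the protocol rule out all records before 2012, because Covariates reaches back 10 years. Look-back for doses is simply unstated. The gap does not depend on it: a person vaccinated in 2015 and diagnosed in 2020 is inside the window and still has no assigned state.

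Finally, an article condenses a fuller plan, and the figures are not available here. That excuses missing detail on dates. It does less for the model, where entry point, states and exclusions are all set out and leave no place for these people.

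**Conclusion.** The concern holds for the multistate model. As written, people already holding doses at diagnosis enter as undosed and at risk, which biases the dose-1 and dose-2 transitions. If they are not dosed again, the dose-1 rate is about 0.63 to 0.95 of its true value, for an assumed 5% to 30% vaccinated beforehand and assumed uptake of 2% to 10% a year. If some are boosted and the booster is read as dose 1, false events offset part or all of that loss, so the net direction for dose 1 is not fixed. Disparity estimates are biased only if earlier vaccination differs between groups, on which the protocol gives no data.

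For coverage the conclusion is conditional. The yearly denominator is undefined. If it is the 2012-2022 newly diagnosed cohort without a fixed follow-up time, constant uptake produces an artificial trend: upwards if the cohort accumulates, downwards if tabulated by diagnosis year. The protocol does not commit to that reading, so a false trend or an undercount of coverage is not established.

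**What to change.** **Model.** Extract all hepatitis A vaccine records at any earlier date available in the same database. Start each person in the state held at CLD diagnosis, with 0 or 1 dose. Count people with two doses in coverage, but leave them out of the transition model. Keep the actual date of dose 1, so that the 12-month and 3-year definitions of dose 2 run from the real first dose.

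**Coverage.** For each year, take as denominator everyone alive and registered on a fixed date with any earlier CLD code, and as numerator those with 1 or 2 doses by that date. For the newly diagnosed cohort, report cumulative incidence of each dose at fixed times from diagnosis (for example 1, 2 and 3 years), by year of diagnosis. Align the Abstract and Study Population wording on whether long-standing cases are included.

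**Cost.** Wider extraction dates, some extra analysis and revised text, with no contact with participants. Older vaccine records are likely to be less complete, so some earlier doses will still be missed; this should be reported as a limitation. The change is cheapest before data extraction.
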